### Recruitment, baseline assessment and randomization

The study coordinator recruits patients by reviewing a list of patients each week who are scheduled for upcoming TKR surgery, assessing patient's eligibility, calling patients to introduce the study and then mailing the consent form. The coordinator then follows up via telephone call. Patients complete and mail back a baseline assessment that includes the SF-36, the Pre-Surgery WOMAC, and a modified arthritis and exercise Self-Efficacy Scale. In addition, participants wear an ankle accelerometer (Step Activity Monitor) for four continuous days (at least one weekend day), and complete an exercise log.

Upon completing the baseline assessment, each patient is randomized into the Patient Self-Management Support intervention or to a usual care (control) condition. The study uses a stratified simple random sampling (S-SRS) of TKR patients to assure that participants represent subgroups of patients who may respond differently to the intervention. Patients are stratified by gender (two categories), BMI (three categories, < 30, 30-35, and > 35), and emotional health (SF36/Mental Composite Score; MCS) (three categories, < 45, 46-60, and > 60). This sampling scheme ensures that the sample includes wide variation in pre-operative BMI and MCS and gender balance. The categories are based on the distribution of pre-operative measures in a national sample. There are 2 × 3 × 3 = 18 strata in total. Within each stratum, 5 patients are randomized to intervention group and 5 to control group. The order of the two blocks is randomly permuted. Total target enrollment for the trial is 180 patients.

### Study conditions

#### Patient Self-Management Support intervention condition

##### Intervention theoretical framework

The intervention is based on social cognitive theory (SCT) [10]. Consistent with SCT, the intervention targets knowledge, attitudes (self-efficacy), and behavioral capabilities for self-management through a variety of literacy- and age-sensitive print materials and activities. The intervention sessions are delivered in accordance with the Patient-Centered Model [11-16], also known as the 5As model. This model guides the interventionist to deliver health behavior change counseling in a brief and structured manner. Accordingly, the counselor Asks about the patient's "*agenda*" for the encounter; *Assesses *the patient's experiences with specific behaviors (often milestone behaviors); *Advises *changes needed for improvement; *Assists *in setting goals for increasing activities and exercise and problem-solves with the individual potential challenges to goal attainment; and *Arranges *follow up. The counselor facilitates and reinforces self-efficacy for specific behaviors by progressively building on the patient's prior successes with the same or similar behaviors, assisting the patient in finding solutions for challenges encountered along the way, encouraging the patient to go a step further, and assisting the patient in eliciting the appropriate support from his or her social environment. Principles of motivational interviewing are used to facilitate the communication between the counselor and the patient [17]. This includes an emphasis on supportive (as opposed to confrontative) exchanges, exploring patient ambivalence and "rolling with resistance."

##### Intervention development

The intervention development was theory-based and its content was informed by thorough literature review of interventions for osteoarthritis arthritis, Internet-based health information, and interviews with TKR surgeons, hospital nurses, hospital- and community-based physical and occupational therapists, and interviews with patients. Challenges to successful post-TKR functional achievement were identified and strategies to address them were developed and integrated to form the intervention. Telephone counseling was selected as the primary basis for the intervention because it is a low-cost, broad reach mechanism for the delivery of post-TKR support interventions to patients with movement limitations and transportation difficulties. Although this counseling format has not been studied among TKR patients, it has been well studied for medical patients with other conditions and has been used alone or in combination with in-person sessions and print materials [18-20]. The initial intervention was further refined following a pre-test with 6 pilot patients.

##### Intervention Structure and Content

The final intervention protocol includes a total of 12 sessions: three prior to surgery, one call the evening before surgery, a hospital visit at 2-3 days after surgery, and seven additional sessions post-discharge between weeks two and nine post-surgery. All sessions, except for the hospital visit are telephone-based. The first call is approximately 45 minutes on average, with follow up contacts ranging from 5 to 20 minutes.

The intervention aims to build self-management skills through the implementation of behavioral strategies. In accordance with the 5As model described above, at each contact the coach and the patient discuss a clear *Agenda*, and the coach *Assesses *knowledge needs, attitudes toward surgery or rehabilitation process (i.e., self-efficacy), and patients' physical activity and exercise behaviors. The counselor delivers brief personalized *Advice, Assists *patients in identifying exercise and physical activity goals and creating an action plan, and *Arranges *follow up. All patients receive the following print materials: benchmarks for recovery, tips for regaining the use of the knee, goal-setting and monitoring forms, and tips on setting goals. Additional intervention materials include a "Toolkit" of one-page print materials that the coach can mail to participants to reinforce strategies or address patient questions or concerns. Pre-surgery coaching topics include: communicating with health care providers and making the most of medical appointments, asking for help from family and friends, where to go after leaving the hospital, tips for choosing a rehabilitation center, sleeping well away from home, understanding the risk of infection, and tips to tracking exercises by using an exercise log. Hospital-related topics include: managing pain in the hospital, help with pain after the hospital, fear of pain medication, conquering constipation, using a continuous passive motion (CPM) machine, breathing well in the hospital and what to do if having trouble breathing, things that can get in the way of recovery, taking care of the incision and scar, helping with swelling, and benefits of ongoing physical activity. Post-surgery topics include: walking again, using a stationary bicycle, physical activity at home, ongoing physical activity, activities that may be limited after the surgery, using exercise and activity logs, joining local groups for physical activity, eating for recovery, and how to tell if making progress. Topics related to emotional health include: tips to help with anxiety, depression, fatigue, and stress. The intervention is delivered in English and Spanish by a trained bilingual health educator. Figure 1 depicts components of the intervention protocol over time.

**Figure 1 F1:**
[figure not shown]
**Counseling Algorithm Enhancing Functional Outcomes of Patients Undergoing Total Knee Replacement Surgery**.

##### Intervention fidelity

Several procedures are implemented to maximize intervention fidelity. The intervention coach was trained in the delivery of the intervention protocol by the investigators. A customized Microsoft Access database guides the delivery of specific intervention components (5A's, as described above). Calls are audiotaped for random review by the behavioral researcher who provides timely feedback to the coach concerning errors of omission or commission, and additional training as needed.

##### Participant safety

A Safety Monitoring Plan is followed. All adverse events are first reported to the PI, the lead surgeon, and the lead behavioral scientist for appropriate action. All serious adverse events (such as hospitalizations), and other adverse events (depression) are reported to the Safety Officer and to the sponsor, NIAMS. Patients who express significant depressive symptoms either to the study Coach or study coordinator, or have a CES-D score ≥ 16, are encouraged to discuss their feelings with their health care provider and to seek professional help. The study team (physical therapist, psychologist and PI) provides consultation and supervision on medical, rehabilitative and psychosocial issues to the coach throughout the program.

#### Control Condition

The control condition consists of usual care as prescribed by the participant's health care providers, including surgical management and physical therapy. Patients in the control condition also receive the copy of standard post-TKR exercises and one goal planning sheet. The surgeon and treating physical therapist are blinded to the study condition and do not participate in data collection of study end-points. However, it is possible for patients to mention the study coach calls to the surgeon at a follow-up visit.

#### Study assessments

Data are collected at baseline prior to surgery and at 8 weeks, 6 months, and 12 months post-TKR. Sources of data include: (1) patients, (2) surgical records, (3) physical therapy records, and (4) data recorded by the intervention coach in the intervention database. The following section describes individual measures used to assess outcomes of interest.

#### Main outcomes

##### Physical Function

The SF-36 Version 2, a generic 36 item assessment of health status is used to assess physical (PCS) and mental (MCS) function [21-24].

##### Knee Function

WOMAC, a 17 item survey, is used to assess knee-specific measures of the degree of difficulty in performing daily activities (e.g., descending stairs) plus joint-specific pain and stiffness [25].

#### Secondary outcomes

Knee performance measures include timed up and go (TUG), timed stairs, and 6 minute walk [26,27]. Knee impairment measures include knee range of motion (ROM) and measurements of knee flexion and extension ROM [28,29]. These measures are collected by trained physical therapists with demonstrated clinically acceptable reliability.

#### Mediators

##### Self-Efficacy

The Stanford Patient Education Research Center Arthritis Self-Efficacy tool was modified slightly to address the post-surgical experience [30]. Scale items assess an individual's perceived ability to manage pain/discomfort and frustration, and keep knee pain from interfering with roles and activities.

##### Exercise and Activity

A *Step Activity Monitor *(accelerometer) assesses mean steps per day and activity intensity (steps per minute). The monitor provides a summary of total number of steps/cycle per 24 hour period and percent time/day that the individual is active at high/moderate/low activity, % of day inactive, and maximum sustained intensity for 5 and 30 minutes [31]. In addition, participants complete an *exercise (paper) log *to record the number of daily exercise sessions, repetitions and sets for each of the core home-based physical therapy exercises. The log is completed at 8 weeks and 6 months.

#### Potential moderators

In addition to the above measures, the study assesses participants' demographic and psychosocial characteristics (i.e., age, gender, residence/zip code, race/ethnicity, educational level, employment, insurance status, depressive symptoms [32], trait anxiety [33], physical co-morbid conditions [34], social support [35,36], and body mass index (BMI).

#### Sample size considerations and statistical analyses

##### Sample size estimation

Sample sizes were calculated using the method developed by Frison and Pocock [37] with the SF-36 PCS as the primary outcome. Because patients are randomized within surgeon, we assume complete randomization of the study subjects to each treatment arm. We used the mean changes of repeated measures to estimate the required sample sizes based on Analysis of Covariance (ANCOVA) method. The mean change is defined as the difference between each subject's mean post-treatment PCS (the mean of 6 and 12 month PCS) and the baseline measurement.

##### Effect Size

This trial was designed to determine whether the intervention will outperform the control by 4 or more points in the SF36 PCS. This effect size is approximately one-half of the PCS standard deviation and 40% of the mean pre-post PCS TKR change of 10.5 points reported in the PORT study. Based on our pilot data and the national registry of TKR patients, mean post-PCS scores are assumed to be 39.5 and 43.5 for the control and intervention arms, respectively; the standard deviation of post-TKR PCS is estimated as 10.9 for pre-and post-intervention periods and the autocorrelation coefficient between the post treatment measurements across time for PCS is 0.65, and between pre-and post treatment measures is 0.50 [4]. One pre-intervention and two post-intervention measurements were completed (6 and 12 months). Assuming 75 completers per condition after attrition or exclusion due to missing data, the trial is capable of detecting an intervention effect of a change of 4 or more points on the SF36 PCS with statistical power in excess of 0.83 at two-sided significance level of 0.05, or 0.90 at one-sided significance level of 0.05. Secondarily, a 10 point difference in change in WOMAC physical functional scores between the arms can be detected with > 85% power at 5% significance level.

##### Analysis Plan

We will test the self-care support program's effect, both overall and in the latent low and high function response groups, as predicted by baseline characteristics on post-TKR 6 and 12 month functional outcome. We will apply mixture models with two latent classes (or GLLAMM), where the post-operative change in global function (PCS/SF36) at 6 or12 months is the primary outcome. The main predictors of the model include intervention indicator (0 = control versus 1 = intervention), data collection time points, and the interaction term between intervention indicator and time points. The treatment effects will be evaluated by testing the significance of the coefficient of intervention indicator and an interaction term of time and the intervention indicator. In the analysis, we will adjust for other patient characteristics that may moderate the intervention effect or reduce unexplained variability including gender, age, baseline function score, BMI, depression, anxiety, or social support. Potential moderating effects of each variable on the intervention will be examined by including interaction terms with the intervention indicator. The intervention effects on changes in knee pain, function using WOMAC sub-scores, number of daily repetitions and mean steps/hour on step activity monitor, and self-efficacy scores) will be analyzed using similar approaches. If the proposed intervention is effective, the post-TKR increases in home exercise and activity levels, and self-efficacy score in the intervention condition should be significantly greater than in the control condition. Next, we will examine whether the improvement in Stanford Arthritis Self-Efficacy scores predicts increases in home exercise and activity levels. Using a similar approach, we will test whether higher levels of home exercise (number of daily repetitions) and physical activity (mean steps/day on accelerometer) at 8 weeks post-TKR are associated with greater improvement in 6 and 12 month post-TKR global physical function and knee function.

In the analysis, we will assess possible selection bias by evaluating the equivalence in subjects' socio-demographic characteristics and baseline clinical and behavioral measures between "completers" (i.e., patients participating in 6 and/or 12 month follow-up) and drop-outs. If systematic and significant differences are observed, we will apply proper statistical procedures to account for such informative attrition or missingness. (See below) Differences between completers and drop-outs will be acknowledged as limitations to the generalization of study results.

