**Discussion:**

As TKR use expands, it is important to develop methods to identify patients at risk for sub-optimal functional outcome and to effectively intervene with the goal of optimizing functional outcomes. If shown efficacious, this peri-TKR intervention has the potential to change the paradigm for successful post-TKR care. We hypothesize that Patient Self-Management Support to enhance adherence to independent activity and exercise will enhance uniform, optimal improvement in post-TKR function and patient autonomy, the ultimate goals of TKR.

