## Background

The number of primary total knee replacement (TKR) procedures has grown by 73% in the past 10 years [1] and is projected to expand by more than 600% to 3.48 million procedures by 2030 [2]. Several facts are responsible for this increase in use, including (1) the prevalence of knee arthritis parallels the growing numbers of older adults, (2) increasing numbers of working aged adults are choosing TKR [1], and (3) TKR is a cost-effective intervention that reduces and eliminates pain. Despite these encouraging facts, significant variation remains in patient-reported functional improvement after TKR. An estimated 15-38% of patients report minimal functional improvement at 12 months, while another 10% report functional gains up to 3 times the national average [3,4]. Furthermore, our data suggests that the distribution of physical function at 12 months after TKR is bimodal [5]. The mechanism that underlies this varied functional improvement is not understood. While TKR researchers have identified some consistent predictors of poor gains in post-TKR function, no one patient attribute or surgical factor offers a satisfactory explanation for this outcome variation [6]. Importantly, poor emotional health as measured by the Mental Composite Score (MCS) of the SF36 is consistently associated with poor functional gain following TKR [3,4]. The NIH TKR Consensus Panel called for further research to address the role of patient attributes and rehabilitation regimens in functional outcome after TKR.

Exercise and activity improve global and knee-specific function in knee arthritis patients [7] and patient's confidence in their ability to manage their arthritis pain and function has been consistently associated with improved function, exercise, pain control, and self-care [8]. We have examined these associations in our pilot research and our data support a direct relationship between quantity of post-TKR exercise and activity and functional gain after TKR. This relationship was mediated by the patient's emotional health (SF36, MCS) and MCS was directly correlated with self-efficacy for arthritis self-care [9].

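### The only model described for the primary outcome is a two-latent-class mixture, while the power belongs to an ANCOVA; a benefit that moves patients between well-separated response classes could be mostly missed

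*Protocol article*

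**What the plan says.** The Analysis Plan section of the protocol article gives one model for the primary outcome, which is PCS change after surgery, at either follow-up visit: "We will apply mixture models with two latent classes (or GLLAMM"). Treatment is judged by "testing the significance of the coefficient of intervention indicator and an interaction term of time and the intervention indicator". The effect is to be tested "both overall and in the latent low and high function response groups, as predicted by baseline characteristics". The section does not say how the overall effect is obtained from the mixture, or whether arm enters the class-membership part. It lists no test of treatment on class membership.

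The Sample size estimation section sizes the trial differently, "based on Analysis of Covariance (ANCOVA) method", using each patient's mean of the 6- and 12-month PCS and the baseline value. No latent classes appear there.

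The apparent reason for two classes is in the Background: "our data suggests that the distribution of physical function at 12 months after TKR is bimodal". The same section puts the share of patients with minimal improvement at 12 months at 15-38%.

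**The concern.** In a two-class mixture the intervention coefficient is the arm difference given class. If treatment turns would-be low responders into high responders, that benefit appears as a change in class membership, and the coefficient leaves it out. Patients who share a class in the two arms are then no longer the groups that randomisation made comparable.

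This mechanism is plausible here. The Discussion part of the Abstract speaks of identifying patients at risk of a poor functional result and says that the support "will enhance uniform, optimal improvement in post-TKR function". Lifting patients out of the low group is one natural way to achieve that. At stake are whether the main test can detect such a benefit and whether the quoted power describes the test that will be run.

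**Working it through.** **1. Reproduce the stated power.** Inputs from the Effect Size section: SD 10.9, correlation between post-treatment measures 0.65, pre-post correlation 0.50, two post-treatment measures, 75 completers per arm, difference 4.

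- Frison-Pocock ANCOVA variance: SD² × [(1 + (r − 1)ρ_post)/r − ρ_pre²] = 118.81 × [(1 + 0.65)/2 − 0.25] = 118.81 × 0.575 = 68.3, so the effective SD is 8.27.
- Standard error of the difference: 8.265 × √(2/75) = 1.350. Ratio: 4/1.350 = 2.964.
- Two-sided 0.05: Φ(2.964 − 1.960) = 0.842 (stated: above 0.83). One-sided 0.05: Φ(2.964 − 1.645) = 0.906 (stated: 0.90).

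The figure is right, but for the ANCOVA only.

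**2. Simulate the mixture coefficient under the same inputs.** There were 400 trials per scenario with 75 per arm. The outcome was the mean of 6- and 12-month PCS, with the protocol's SD and correlations. Assumed, because the protocol does not give them: class separation D, low-class share in controls, and a log-odds slope of 0.06 per point of baseline PCS for class membership. In the switching scenarios the whole 4 points comes from class membership: D × (fall in low-class share) = 4, for example 16 × (0.38 − 0.13) = 4. The mixture coefficient was tested by likelihood ratio, with class predicted from baseline only or from baseline and arm.

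| Scenario | Low share, control → intervention | ANCOVA power | Mixture power, class on baseline only (mean estimate) | Mixture power, arm also in class model |
|---|---|---|---|---|
| Switching, D = 10 | 45% → 5% | 0.90 | 0.85 (3.9) | 0.14 |
| Switching, D = 12 | 38% → 4.7% | 0.88 | 0.76 (3.5) | 0.11 |
| Switching, D = 14 | 38% → 9.4% | 0.88 | 0.47 (2.3) | 0.06 |
| Switching, D = 16 | 38% → 13% | 0.92 | 0.08 (0.2) | 0.06 |
| Switching, D = 17 | 30% → 6.5% | 0.92 | 0.08 (0.1) | 0.08 |
| Uniform shift, D = 16 | 38% in both | 0.82 | 1.00 (3.9) | 1.00 |

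Monte Carlo error is about ±2 to 5 percentage points. The 45% share lies above the protocol's 15-38%. With arm in the class model, a joint 2-df test of the coefficient and the class effect had power 0.89-0.97 in the switching scenarios. What fails is the coefficient read alone.

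**3. A simpler mixture as a second check.** Class probability was constant, classes were 16 points apart with within-class SD 5, and the low share fell from 40% to 15% (again just outside 15-38%), with 300 runs. Power was 24% against 79% for a comparison of means, and the mean estimate was 1.4 instead of 4. Under a uniform shift it was 96% against 76%.

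**4. Which separations fit a bimodal outcome?** Take two normal classes of equal variance (a simplification). If the SD of the 6/12-month mean is 10.9 × √0.825 = 9.9, two modes appear only from about 15.8 points (38% low) or 16.9 points (30% low). With SD 10.9 for a single time point the thresholds are about 17.4 and 18.6. Even a 50:50 split needs about 14 to 15.5. Separations of 10-12 would not look bimodal.

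**The case against.** The plan does announce an overall test, and a condensed article may leave its form to a fuller document. The classes are said to be predicted by baseline characteristics. If membership is a fixed pre-randomisation type, within-class effects are valid. The alternative named in brackets, GLLAMM, is a broad family, so the exact model is not settled. Powering on a simpler model than the one analysed is common and not in itself an error.

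The large loss also needs nearly pure class switching and wide separation. In a further 200-run check with half the benefit as a shift and half as switching, at 16 points and within-class SD 5, power was 71% against 77% (estimate 2.5). With pure switching at 12 points and SD 7.5 it was 77% against 84%. The Abstract's phrase about uniform improvement does not say that the mechanism is class switching; the stated hypotheses concern greater improvement in function through self-efficacy and exercise. None of the simulations includes the arm-by-time term.

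All of this stands as a limit on the point, but it does not remove it. The overall test has no model, so the marginal comparison of randomised arms is not secured. The fixed-type assumption cannot be tested and conflicts with a benefit that moves patients between classes. Predicting class from baseline did not restore power at 16-17 points.

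**Conclusion.** The point holds conditionally. The one model described for the primary outcome tests a class-conditional coefficient, and the quoted power is for a different analysis. With mainly class-switching benefit and classes about 16 points or more apart, power for a true 4-point effect is about 8-24% against 79-92% for a marginal comparison. At 10-12 points it is 76-85% against 88-90%, provided arm is not in the class model. Under a uniform within-class shift the mixture is the more powerful analysis. Separation, class shares and mechanism are assumptions. The protocol supports them only through its statement on bimodal 12-month function, which is not a statement about PCS change, and its 15-38% range.

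A reader might infer three stronger things that the documents do not support:

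- **That class-specific effects have no causal reading at all.** They have one if treatment does not affect membership, and the text on baseline prediction is compatible with that.
- **That a real benefit will be largely missed.** This depends on the mechanism and the separation.
- **That the mixture test exceeds its 5% level.** In the second simulation the common-effect test rejected in 20 of 300 null runs (6.7%, exact 95% interval 4.1-10.1%), which is compatible with 5%. Only a class-specific 2-df test, which the protocol does not specify, was higher (8.3-9.0%).

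This should be fixed; confidence is moderate.

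**What to change.** Name as primary the comparison of randomised arms that was powered: a baseline-adjusted ANCOVA of the mean of 6- and 12-month PCS, or an equivalent repeated-measures model, adjusted for the stratification factors (gender, BMI category, MCS category). State that this is the overall test.

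Keep the latent-class mixture as secondary or exploratory. Say whether arm enters the class-membership part, and if it does, test that effect together with the within-class coefficient. To study who benefits, use the interaction of arm with a risk of low function predicted from baseline data only.

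The cost is wording; sample size and data collection do not change. The downside is that the mixture loses primary status, and with it the power gain it would have if the benefit were a pure shift within classes.

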**Methods/Design:**

This randomized clinical trial (RCT) will test the efficacy of a theory-based telephone-delivered Patient Self-Management Support intervention that seeks to enhance adherence to independent exercise and activity among post- TKR patients. The intervention consists of 12 sessions, which begin prior to surgery and continue for approximately 9 weeks post-TKR. The intervention condition will be compared to a usual care control condition using a randomized design and a probabilistic sample of men and women. Assessments are conducted at baseline, eight weeks, and six- and twelve- months. The project is being conducted at a large healthcare system in Massachusetts. The study was designed to provide greater than 80% power for detecting a difference of 4 points in physical function (SF36/Physical Component Score) between conditions (standard deviation of 10) at six months with secondary outcomes collected at one year, assuming a loss to follow up rate of no more than 15%.

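### The primary PCS comparison is stated in three different ways and judged on two coefficients with no rule for combining them; the stated power fits only the mean of the 6- and 12-month scores

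*Protocol article*

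**What the plan says.** The protocol article describes the primary comparison in three places.

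- **Abstract, Methods/Design.** More than 80% power for a 4-point PCS difference "between conditions (standard deviation of 10) at six months with secondary outcomes collected at one year".
- **Sample size estimation and Effect Size.** The quantity powered by ANCOVA is "the difference between each subject's mean post-treatment PCS (the mean of 6 and 12 month PCS) and the baseline measurement". The SD is 10.9, with 75 completers per arm. Power is given as above 0.83 at two-sided 0.05, "or 0.90 at one-sided significance level of 0.05".
- **Analysis Plan.** In a mixture model with two latent classes, "the post-operative change in global function (PCS/SF36) at 6 or12 months is the primary outcome". The predictors are arm (0/1), time point and their interaction. The treatment effect is evaluated by "testing the significance of the coefficient of intervention indicator and an interaction term of time and the intervention indicator". The effect is also to be tested overall and within the low and high latent response groups.

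The article does not say which visit is the reference, how time is coded, whether the two coefficients are tested jointly or separately, or which result decides the trial.

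**The concern.** These are different comparisons. The Abstract makes 12 months secondary, whereas the sample-size section gives it half the weight of the primary measure. The wording in the Analysis Plan would admit either visit.

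The two named coefficients also answer different questions. If time is categorical with one visit as reference, the arm coefficient in a model containing arm × time is the effect at that visit only. It equals the average over both visits only if time is centred. The interaction asks whether the effect changes between 6 and 12 months. It does not ask whether patients benefit, and a constant benefit leaves it at zero.

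Two things are at stake. If the choice among these results is made after the data are seen, the nominal 5% error rate is not protected. If the test finally used is not the averaged contrast, the trial may have less power than it reports.

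**Working it through.** **Inputs (Effect Size, unless noted).** Difference 4; SD 10.9 (Abstract: 10); correlation between the two post-operative scores 0.65; baseline to post-operative correlation 0.50; one baseline and two post-operative measurements; 75 completers per arm. All calculations use a plain normal model with baseline adjustment and a constant 4-point effect. They do not represent the latent-class model itself.

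**1. The plan's own figure.** ANCOVA variance factor for the mean of two visits: (1 + 0.65)/2 − 0.50² = 0.825 − 0.25 = 0.575.
- Effective SD = 10.9 × √0.575 = 8.265.
- SE = 8.265 × √(2/75) = 1.350.
- z = 4/1.350 = 2.964.
- Two-sided power = Φ(2.964 − 1.960) = 0.842. One-sided power = Φ(2.964 − 1.645) = 0.906.

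Both stated values reproduce. A change score without ANCOVA adjustment gives 0.696, so the stated power belongs to the baseline-adjusted averaged contrast.

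**2. Arm coefficient at a single visit.** Variance factor 1 − 0.50² = 0.75.
- SD 10.9: effective SD 9.440, SE 1.541, z = 2.595, power Φ(0.635) = 0.737.
- SD 10: effective SD 8.660, SE 1.414, z = 2.828, power Φ(0.868) = 0.807.

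The Abstract's claim of more than 80% at six months therefore reproduces with its own SD, but not with the SD in Effect Size.

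**3. Joint test of both coefficients (2 df).** With a constant effect the interaction contributes nothing. The noncentrality is that of the averaged contrast, 2.964² = 8.78, spread over two degrees of freedom. Power is 0.760.

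**4. False-positive rate by decision rule.** After baseline adjustment the correlation between the 6- and 12-month effects is (0.65 − 0.25)/(1 − 0.25) = 0.533. With 6 months as reference, the correlation of the arm coefficient with the interaction is −√((1 − 0.533)/2) = −0.483. Simulation of correlated normal statistics, each tested at two-sided 0.05, gives:

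| Rule for success | Type I error |
|---|---|
| Joint 2-df test | 5% (by construction) |
| Both coefficients significant | 0.9% |
| Either visit significant | 9.0% |
| Either coefficient significant | 9.1% |
| Any of 6 months, 12 months, interaction | 12.2% |

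With centred time the two coefficients are independent, and the either-coefficient rate is 1 − 0.95² = 9.75%.

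**The case against.** The strongest reply is that this is a condensed article. Time coding, reference visit, joint or separate testing and multiplicity are commonly left to the analysis plan, which is not shown. That stands for those details taken alone. It does not cover the primary comparison, which the article itself states more than once and not consistently. A later document could choose among the statements but could not make them agree.

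A reader might infer more than the text supports:

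- **That the false-positive rate is 9% to 12%.** No section says that one significant result is enough. The sentence on the two coefficients equally permits a joint test. The upper figure also needs a third test beyond the two coefficients named.
- **That the stated power belongs to no test in the Analysis Plan.** With centred time the arm coefficient is the powered contrast, and the plan leaves time coding open. If 6 months is the reference, the arm coefficient is the Abstract's endpoint, whose power reproduces at SD 10.
- **That a constant benefit would almost always fail.** This requires a rule that both coefficients be significant, which no section states.
- **That a one-sided test is planned.** The one-sided figure is an additional power statement, and the two-sided level comes first.

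It is also fair that the repeated-measures structure can deliver the mean of the two visits, and that the phrase about 6 or 12 months may be loose wording, since the same section opens by referring to both. The sharpest conflict is between the Abstract and the sample-size section.

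**Conclusion.** The concern holds as an inconsistency with a conditional cost. The primary comparison is not fixed, and the combination rule for the two coefficients is unstated. The stated power is correct, but only for the baseline-adjusted mean of two visits. Depending on the reading, the type I error runs from about 0.9% to about 12%. At SD 10.9, power is 0.84 for the averaged contrast, 0.76 for the joint test and 0.74 for a single visit.

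These sizes rest on the plan's SD and correlations, 75 completers per arm, a constant 4-point effect and a normal model. The two-class mixture model could behave differently, and the documents give nothing from which to quantify that. The point should be settled before outcome data are compared by arm, because the trial's conclusion could turn on which version is used.

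**What to change.** Name one primary contrast and use it in every section. The natural choice is the one already powered: the between-arm difference in the mean of 6- and 12-month PCS, adjusted for baseline PCS, tested once at two-sided 0.05. In the repeated-measures model this is the arm effect averaged over the two visits, and it should be written as that contrast so that the result does not depend on how time is coded.

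Make the 6-month, 12-month, arm × time and latent-class results secondary. Align the Abstract, Sample size estimation, Effect Size and Analysis Plan, including the SD (10 or 10.9). State that the primary test is two-sided.

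Six months could be named instead, but its power at SD 10.9 is 0.74. Reaching 80% would take 88 completers per arm out of the 90 per arm implied by the target of 180.

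The cost is wording only, with no new patients or data. The downside of the preferred choice is that a significant result at one visit alone would no longer count as primary success.
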